### Benefits

The intervention is expected to suppress T-cell reactivity to CRYAB, and as a consequence, halt the formation of new inflammatory demyelinating MS lesions. As evidenced by animal model data, as well as by preliminary Phase I data on human tetanus toxoid responses, the intervention is antigen-specific, or at least largely antigen specific. For this reason, DC-TAB is not expected to impact in any way on peripheral immune reactivity against any other antigen. Relative to current disease-modifying drugs in MS, which all involve general immune modulation, treatment with DC-TAB, when successful, will thus offer an improved level of selectivity, and is not expected to suffer from side effects due to any general immune-modulatory activity.

# Study objectives

## Primary Objective

To evaluate the safety and tolerability of three single doses of DC-TAB administered intravenously with 2-months intervals in patients with multiple sclerosis.

## Secondary objectives

1. To evaluate the antigen-specific T-cell tolerance inducting effect of three single doses of DC-TAB administered intravenously with 2-months intervals in patients with multiple sclerosis.
2. To evaluate the clinical effects of three single doses of DC-TAB with 2-months intervals administered intravenously in patients with multiple sclerosis.
3. To evaluate the pharmacokinetics of DC-TAB in patients with multiple sclerosis.
4. To evaluate the effects of three single doses of DC-TAB with 2-month intervals administered intravenously to patients with multiple sclerosis on serum levels of CRYAB/DC-TAB-reactive antibodies.

# Investigational plan

## Overall study design and plan – description

This study is a randomized, double-blind, placebo-controlled, exploratory, dose-ranging Phase IIa study to evaluate the safety, tolerability, T-cell tolerance inducing effect, clinical effects, pharmacokinetics, and effects on serum antibodies of human alpha B-crystallin (CRYAB), the active ingredient of DC-TAB.

Patients who fulfill all eligibility criteria will be randomized to one of the treatments, placebo, 7.5 mg DC-TAB, 12.5 mg DC-TAB or 17.5 mg DC-TAB in a 1:1:1:1 fashion. Patients will receive a single i.v. bolus injection treatment which will be repeated twice with 2-month intervals during the 6-month monitoring period. By a single intravenous bolus administration of DC-TAB, a state of T-cell tolerance is expected to be established within days. Each month, T-cell responses to DC-TAB will be assessed (the results of which will be known two weeks after blood sampling). The interval period between treatments may be adjusted in case the duration of the tolerizing effect in patients is different from what is currently expected.

The study consists of two parts, a treatment period of 24 weeks and a follow up period of an additional 24 weeks. Patients will return to the hospital weekly during the first month, and monthly thereafter.

The primary analysis will be performed on the treatment period, i.e. after all patients have completed 24 weeks; an additional analysis will be performed once all patients have completed the study. Patients and site study personnel will remain blinded throughout the study.

After 12 and 24 patients have completed 4 and 12 weeks of follow-up, a partially blinded safety review will be conducted by the DMC to verify safety and adequate tolerization by the intervention in MS patients.

## Study flow chart

Figure 4‑1 Study flow chart

|  |  |  | | | |  |  |
| --- | --- | --- | --- | --- | --- | --- | --- |
|  | | DC-TAB 7.5 mg | | | |  | |
| Screening | | DC-TAB 12.5 mg | | | | Follow-up | |
|  |  | DC-TAB 17.5 mg | | | |  |  |
|  |  | Placebo | | | |  |  |
|  |  |  |  |  |  |  |  |
|  | Rx | Rx | Rx |  |  |  |  |

## Discussion of study design, including choice of control groups

A double-blind, parallel design has been chosen to minimize the chance of bias.

Inclusion of a placebo control group will allow for a minimum of bias, and a correction for possible placebo effects. As patient’s clinical status is frequently checked, and since the use of certain other frequently used disease-modifying MS treatments like interferon-beta and glatiramer acetate is allowed during the course of the study, the use of a placebo control group is considered ethical.

As this study is the first study in patients, the number of patients per treatment group for this study is not based on statistical considerations, but based on medical/scientific and practical grounds.

A DSMB will be established to further secure patient safety as this is the first-in-patient study conducted with DC-TAB.

## Study population

Thirty-two (32) male and female patients with relapsing multiple sclerosis between 18 and 55 years of age.

### Inclusion criteria

1. Clinically definite relapsing multiple sclerosis, according to the McDonald criteria
2. Abnormal MRI consistent with MS
3. Neurologically stable for at least one month
4. At least one clinical relapse over the previous year, or two relapses over the past two years, or one or more gadolinium-enhancing MRI lesion(s) at the time of screening.
5. An EDSS score ≤ 5.5
6. Age 18-55 years
7. Body weight less than 130 kg
8. Use of adequate and stable contraception for 3 months prior to study initiation, during the course of the study and 30 days thereafter. Sexually active males must use a condom. Sexually active females must use double-barrier contraception or hormonal contraceptive (oral, transdermal, vaginal ring, implants), or must have undergone clinically documented total hysterectomy and/or oophorectomy, surgical sterilization, or be postmenopausal defined by amenorrhea for at least 12 months and confirmed with a FSH ≥ 40 mIU/ml.
9. If patients claim abstinence as their method of contraception, they must be willing to agree to use condoms if they become sexually active from 14 days prior to the first dose of the study drug through 90 days beyond the conclusion of the study.
10. Being informed of the nature and aims of the study, and having given written consent to participate in this study in accordance with local laws and requirements
11. Being willing to comply with the protocol, and understand the information given, and the text of the consent form

### Exclusion criteria

1. Primary progressive multiple sclerosis
2. Use of systemic corticosteroid treatment for more than 3 days within 30 days prior to screening
3. Plasmapheresis, or intravenous gammaglobulins less than 2 months before screening
4. Treatment with natalizumab less than one year before screening
5. Previous immunosuppressive treatment (e.g. cyclophosphamide or mitoxantrone)
6. Previous treatment with any leukocyte-targeting monoclonal antibody (e.g. rituximab, alemtuzumab, daclizumab)
7. Previous treatment with oral immune-modulatory agents (cladribine, fingolimod, laquinimod, fumarate)
8. Pregnant women, women planning to become pregnant and breastfeeding women
9. A history of or currently active clinically significant cardiac (including clinically significant ECG abnormalities in the opinion of the PI), pulmonary, gastrointestinal, hepatic, renal, pancreatic, or neurological disease
10. ALT, AST and/or gamma-GT above 3 times the upper limit of normal
11. Serum creatinine above 1.5 times the upper limit of normal or an eGFR < 60 ml/min/1.73 m^2^
12. Hemoglobin < 7.0 mmol/l for females and < 8 mmol/l for males; leucocytes > 20*10^9^/l or < 3.5*10^9^/l; platelets < 125*10^9^/l
13. SBP > 160 mmHg and/or DBP > 100 mmHg
14. Acute respiratory or other active infections
15. Fever (body temperature > 38.0 °C on day 1
16. Blood donation or significant blood loss within 90 days of first study medication dosing
17. Plasma donation within 7 days of first study medication dosing
18. Recipients of blood or blood products in the last 6 months
19. Participation in another clinical study within 90 days of the start of this trial or planning participation in another clinical trial during this study or in the 4 weeks after last visit
20. Taking anti-coagulation or anti-platelet medication with the exception of NSAID’s.
21. History of drug addiction (positive drug screen) or excessive use of alcohol (weekly intake more than 28 units of alcohol), or psychological or other emotional problems that are likely to invalidate informed consent, or limit the ability of the patient to comply with the protocol requirements
22. Vaccination with any vaccine within 4 weeks prior to dosing of the study medication
23. History of serious adverse reactions or hypersensitivity to any medicinal product
24. History of a malignancy other than skin cell basalioma 5 years prior to screening
25. Any physical condition that would, in the opinion of the investigator, place the patient at an unacceptable health risk or risk of injury or render the patient unable to meet the requirements of the protocol

### Excluded prior and concomitant treatments

The following medication is prohibited throughout the study:

1. High-dose systemic corticosteroid treatment unless given for treatment of relapses
2. Plasmapheresis, or intravenous gammaglobulins
3. Treatment with natalizumab
4. Immunosuppressive treatment (e.g. cyclophosphamide or mitoxantrone)
5. Treatment with any leukocyte-targeting monoclonal antibody (e.g. rituximab, alemtuzumab, daclizumab)
6. Treatment with oral immune-modulatory agents (cladribine, fingolimod, laquinimod, fumarate)

Treatment with other disease-modifying agents such as interferon-beta and glatiramer acetate should be avoided as much as possible, but are allowed if the investigator considers it necessary for these agents to be given.

Should any treatment / medication, prescription and/or OTC, other than the investigational products be necessary for treatment of adverse events, the disease or as prophylaxis, the investigator must note the use of concomitant medication in the source documentation and the CRF. This record should include the drug name (trade name), the total daily dose, route of administration, the start and stop date of administration, and the indication for use (which should match the AE text for which the concomitant medication was administered).

### Withdrawal of patients

A treatment withdrawal is a patient who stops treatment prematurely (for any reason).

If, during the course of the study, there is deterioration in the patient’s well being or the investigator feels that it is in the patient’s best interest to be stop study treatment, the patient treatment can be discontinued. In case a serious adverse event related to the study medication occurs, the study treatment must be stopped permanently for this patient, unless doing so would harm the patient in the opinion of the investigator.

The patient has the right to stop study treatment or completely withdraw from the study at any time and for any reason.

All patients discontinuing study treatment should have a final visit including at least all safety assessments (see also section 6.3). Reasons for patient withdrawal will be documented in the CRF.

Patients withdrawn or stopping treatment after first administration of study medication will not be replaced. Patients withdrawn prior to first administration of study medication will be replaced.

### Pausing and premature termination of the study

In case of safety or tolerability concerns, the sponsor may decide to temporarily pause recruitment of patients in the trial and/or study drug administration. When the trial is temporarily paused, the Competent Authorities (CA) and Ethics Committee will be notified immediately (but at least within 15 days from when the trial is temporarily paused). The notification will be made as a substantial amendment using the Notification of Amendment form and clearly explaining what has been halted (e.g. stopping recruitment and/or interrupting treatment of patients already included) and the reasons for the temporary pause.

Recruitment and study drug administration would resume only if review of the adverse events that caused the pause resulted in a recommendation from the review committee to permit continuation of the study. To restart a trial that has been temporarily halted, the sponsor will make the request as a substantial amendment using the Notification of Amendment form and by providing evidence that it is safe to restart the trial.

If the clinical observations in the study suggest that it may be unwise to continue, the study may be prematurely terminated by the sponsor. If the sponsor decides not to recommence a temporarily halted trial, the CA and Ethics Committees will be notified within 15 days of his decision, using the End of Trial Declaration form and including a brief explanation of the reasons for ending the trial. Additionally, the trial may be terminated by the sponsor at any time for administrative reasons.

Delta Crystallon BV. may stop the study at a specific center for any of the following reasons:

- The center cannot include an adequate number of patients
- Serious and/or persistent non-compliance with the protocol
- Careless or premeditated false documentation in the CRF
- Inadequate co-operation with Delta Crystallon BV or its representatives
- Non-compliance with GCP and / or regulatory requirements
- The investigator requests discontinuation

Delta Crystallon BV has the right to close this study at any time, although this should occur only after mutual consultation. Should the study be closed prematurely, all study materials (for example completed, partially completed and blank CRFs and all unused investigational products) must be returned to Delta Crystallon BV.

Reasons that may require termination of the study include, but are not limited to:

- Enrolment of patients is unsatisfactory
- Quality of data is unsatisfactory
- Data recording is inaccurate and / or incomplete on a chronic basis
- The incidence and / or severity of AEs indicate a potential health hazard caused by treatment with the investigational products
- Completed accrual and follow-up of patients

# Treatments

## Treatments administered

The pharmacy or an unblinded nurse not involved in clinical conduct of the study will prepare all study medication for all patients according to the treatment randomization list.

Patients will receive a single dose of study medication as intravenous bolus injection administered in the arm every two months, for a total of three times during the study. The required amount of study medication will be administered over 30 seconds to the patient via an intravenous catheter.

## Selection of doses in the study

Based on Phase I data on the T-cell tolerizing effect of a single intravenous administration of DC-TAB, the effective dose in MS patients is expected to be approximately 0.2 mg/kg, or a fixed dose of approximately 12.5 mg per injection.

The NOAEL observed in rats following 28 days treatment was set at 17.5 mg/kg, which is equivalent to an HED of 3.2 mg/kg.

The NOAEL in female dogs could not be established following 15 days of treatment, whereas the NOAEL established for male dogs was 0.5 mg/kg following 15 consecutive dose administrations. The NOAEL for up to 5 days treatment was set at 12 mg/kg for both female and male dogs.

In healthy volunteers, single doses as well as three consecutive daily intravenous doses up to 37.5 mg were well tolerated and safe. Most commonly noted adverse drug reactions were local irritability and thrombophlebitis at the injection site.

In healthy volunteers, a single dose of 12.5 mg induced a statistically significant suppression of CD4+ and CD45RO+ T-cell responses to DC-TAB, in half the subjects to levels considered to reflect non-responsiveness. This immunological effect is expected to provide a clinical effect in MS patients. Suppression of T-cells was established within 8 days and maintained for 28 days, but had partially reversed after 6-8 months. In addition to the selection of 12.5 mg, one dose level above 12.5 mg (i.e. 17.5 mg) and one dose level below 12.5 mg (i.e. 7.5 mg) was selected for this study to further obtain information on the optimal dose. Given the currently information on the half-life of inducible regulatory T cells, the tolerizing effect is expected to be maintained for approximately 2-3 months after dosing. Therefore, dosing is repeated twice with 2-month intervals.

## Methods of assigning patients to treatment groups

Apart from his/her patient screening number, each patient whose eligibility has been confirmed will be allocated a sequential randomization number at site level. Patients will be assigned to a treatment code prepared by the CRO.

## Blinding procedures

Sealed treatment randomization codes should be stored in the Investigator’s File or any other secure place at the investigator’s site.

Unblinding of the codes should only be done after closing the database, or in case of emergency. Premature unblinding should always be documented and explained on the code envelope.

At regular intervals and after completion of the study, the code envelopes will be checked by the monitor for intactness.

The syringe will be prepared by the pharmacist or an unblinded nurse who is not involved in the clinical conduct of the study. In order to maintain blinding, syringes will be covered in non-transparant foil to avoid identification of the compound based on a slight difference in colour between the active IMP and placebo. The labels in the syringes will contain the randomization number, the patients’ initials, and the date and time of preparation of the syringe.

## Treatment compliance

Administration of study medication and any deviation thereof will be recorded in the CRF.

# Conduct of the study

## Screening and selection of patients

The patient will receive verbal and written information concerning the study. The patient should be given adequate time to read the information leaflet and an opportunity to ask the investigator/delegate any questions.

Following the provision of patient information, written consent will be obtained from the patient prior to any study-specific procedure. The patient is not to enter the study if he/she has not understood the written and verbal information provided, and/or has not personally signed and dated the consent form. A copy of the patient information leaflet and the signed informed consent will be provided to the patient and a copy will be retained by the investigator.

Patients who fulfill the selection criteria will be enrolled into the study and enter a screening period to fully assess their suitability for treatment (randomization). The patients will be allocated screening number at enrolment. During this period, patients will be screened according to the inclusion and exclusion criteria and the schedule of assessments (see sections 4.4.1, 4.4.2 and 6.5).

If the assessments at screening do not reveal any condition inconsistent with the inclusion, or consistent with the exclusion criteria, the patient qualifies for treatment. Subsequently the patient will be assigned a randomization number in addition to the patient’s screening number*,* which will ensure unambiguous identification throughout the study.

Patient randomization numbers, in addition to the screening numbers assigned by the center, will be recorded on a patient log, which will be kept on file at the study-site.

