## Schedule of assessments

Table 6‑1 Schedule of assessments

| **Assessment** | **Week -4 to -1 (screening)** | **Day 0** | **Week 1**  **± 1 d** | **Week 2**  **±1 d** | **Week 4**  **± 3 d** | **Week 8**  **± 3 d** | **Week 12**  **± 3 d** | **Week 16**  **± 3 d** | **Week 20**  **± 3 d** | **Week 24 or EoT**  **± 3 d** | **Week 36**  **± 3 d** | **Week 48**  **± 3 d** |
| --- | --- | --- | --- | --- | --- | --- | --- | --- | --- | --- | --- | --- |
| Written consent | x |  |  |  |  |  |  |  |  |  |  |  |
| Inclusion/Exclusion criteria | x |  |  |  |  |  |  |  |  |  |  |  |
| Demographic data | x |  |  |  |  |  |  |  |  |  |  |  |
| Medical History | x |  |  |  |  |  |  |  |  |  |  |  |
| Previous medication | x |  |  |  |  |  |  |  |  |  |  |  |
| Study drug administration^4^ |  | x |  |  |  | x |  | x |  |  |  |  |
| MRI | x |  |  | x | x | x^3^ | x | x^3^ | x | x | x | x |
| EDSS | x | x |  |  |  | x |  | x |  | x | x | x |
| MSIS-29 |  | x |  |  |  | x |  | x |  | x | x | x |
| Neurological evaluation/clinical relapse | x | x | x | x | x | x | x | x | x | x | x | x |
| Blood sample for effect parameters (T-cell response | x | x |  |  | x | x | x | x | x | x | x | x |
| Anti-CRYAB/DC-TAB antibodies | x | x |  |  | x | x | x | x | x | x | x | x |
| Safety Laboratory Tests (Haematology, Biochemistry, Urinalysis) ^6^ | x | x | x |  | x | x |  | x |  | x | x | x |
| Urine Pregnancy Test | x |  |  |  |  | x |  | x |  | x |  |  |
| PK sampling | x^8^ | X^1^ |  |  |  |  |  |  |  |  |  |  |
| Physical examination | x | x | x | x^2^ | x^2^ | x | x^2^ | x | x^2^ | x | x^2^ | x |
| Vital Signs ^7^ | x | x |  |  |  | x |  | x |  | x |  | x |
| Body temperature^7^ | x | x |  |  |  | x |  | x |  |  |  |  |
| 12-Lead ECG | x | x |  |  |  | x |  | x |  | x |  | x |
| Adverse events |  | X^5^ | x | x | x | x^5^ | x | x^5^ | x | x | x | x |
| Concomitant medication |  | x | x | x | x | x | x | x | x | x | x | x |

^1^ Samples (relative to study drug administration) at pre-dose, t=10 minutes, t=20 minutes, t=30 minutes, t=1 hour, t=2 hours, t=4 hours, t=8 hours, t=16 hours, t=24 hours;

^2^ Brief physical examination (symptom guided)

^3^ MRI can be made on dosing days after study drug administration

^4^ On study drug administration visits need patient hospitalization for 24h after dosing.

^5^ Repeated adverse event review is needed 24 hours after each dosing

^6^ See the full list of the laboratory parameters in section 7.2.1.

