### Urine pregnancy tests

Urine pregnancy tests will be performed on all females according to the schedule of assessments (see section 6.5). Pregnancy tests will be performed at the study centre. In the event that the patient is withdrawn, a urine pregnancy test will be performed at the last visit.

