## Reporting of Pregnancy

A newly diagnosed pregnancy in itself will not be considered an AE unless it is suspected that the investigational product(s) interacted with a contraceptive method or had some association with the occurrence of pregnancy. A congenital anomaly as a result of this pregnancy is a serious adverse event (SAE).

Before study enrollment, women of childbearing potential must be advized of the importance of avoiding pregnancy during their study participation. All women of childbearing potential must be willing to undergo a pregnancy test before the first administration of the investigational product.

The investigator must immediately notify the sponsor of any pregnancy associated with the study exposure, including 30 days for females after the study who will forward Pregnancy Surveillance Form(s) for monitoring the outcome of the pregnancy.

In addition, the investigator must report to the sponsor follow-up information regarding the course of the pregnancy, including perinatal and neonatal outcome. Infants will be followed for a minimum of 6 months.

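### Dose 1 is the only one of the three doses without a same-day pregnancy test; two small eligibility wordings should be tidied at the same time

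*Protocol*

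**What the plan says.** **Pregnancy testing.** Section 7.2.2 defers to the visit schedule: "Urine pregnancy tests will be performed on all females according to the schedule of assessments". The Table 6-1 row reads "Urine Pregnancy Test | x | | | | | x | | x | | x", that is, screening, Week 8, Week 16 and Week 24, with Day 0 blank. Section 11.3 adds "All women of childbearing potential must be willing to undergo a pregnancy test before the first administration of the investigational product" but gives no maximum age for that test. Pregnancy is an exclusion (4.4.2, no. 8), and 4.4.1 requires "Use of adequate and stable contraception for 3 months prior to study initiation".

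**Eligibility.** Section 6.1 states "If the assessments at screening do not reveal any condition inconsistent with the inclusion, or consistent with the exclusion criteria, the patient qualifies for treatment". The schedule row is "Inclusion/Exclusion criteria | x", with the single tick at screening. Section 4.1 states "Patients who fulfill all eligibility criteria will be randomized to one of the treatments", and section 5.3 states "each patient whose eligibility has been confirmed will be allocated a sequential randomization number at site level". Section 4.4.2 nevertheless ties four exclusions to the first dose: fever on the dosing day (no. 15), blood donation or significant loss in the 90 days before (no. 16), plasma donation in the 7 days before (no. 17) and vaccination in the 4 weeks before (no. 22).

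**Steroids.** The synopsis excludes a systemic course of 3 or more consecutive days. Section 4.4.2 excludes use exceeding 3 days and does not mention consecutive days. Both look back 30 days from screening.

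**The concern.** The protocol tests for pregnancy on the day of doses 2 and 3, so it evidently regards a same-day result as worth having. The first exposure to the product in each patient goes without one and relies on a result that may be about four weeks old. A pregnancy begun after the screening test, or too early for it to detect, would not be looked for again until Week 8. What is at stake is fetal exposure to an investigational biologic and to gadolinium, which a very cheap test could avoid.

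The two lesser items concern consistent eligibility. A criterion dated to dosing cannot be fully judged at an earlier visit, and no text says when it is confirmed. A steroid course that the synopsis excludes is admitted by the criteria section.

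**Working it through.** No sample-size, power or error-rate figure is involved. The check compares schedule rows and applies the two steroid rules to the same course.

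**1. Doses against tests (Table 6-1).**

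| Row | Screening | Day 0 | Week 8 | Week 16 | Week 24 |
| --- | --- | --- | --- | --- | --- |
| Study drug | – | x | x | x | – |
| Urine pregnancy test | x | – | x | x | x |
| Safety laboratory, including urinalysis | x | x | x | x | x |
| Inclusion/exclusion | x | – | – | – | – |
| Body temperature | x | x | x | x | – |
| Concomitant medication | – | x | x | x | x |
| Medical history | x | – | – | – | – |

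Dosing visits without a same-day pregnancy test: Day 0 only, 1 of 3. A note under the table puts assessments before dosing unless otherwise stated, so the tests at Weeks 8 and 16 precede doses 2 and 3. Urine is already collected on Day 0.

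**2. Age of the test at dose 1.** The screening column spans Week -4 to Week -1.
- Upper end: 4 × 7 = 28 days.
- Lower end: 7 days if Week -1 means one week before dosing; about 1 day if it means the week leading up to dosing. The protocol does not say which.

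The age is therefore up to about 28 days, with a minimum between about 1 and 7 days. At doses 2 and 3 it is 0 days.

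**3. Time to the next scheduled test.** Week 8 is 8 × 7 = 56 days after Day 0 (visit window ±3 days). Counted from the screening test, the interval is at most 28 + 56 = 84 days, ignoring the window. Dose 1 and the gadolinium scans at Weeks 2 and 4 (Table 6-1, section 7.4.3) fall inside it.

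**4. Exclusions dated to dosing.**
- No. 15, fever: the Day 0 pre-dose temperature can serve.
- No. 22, vaccination: the Day 0 concomitant-medication record can serve if the question is asked.
- Nos. 16 and 17, blood and plasma donation: no Day 0 row asks about donation, and medical history is taken only at screening.

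How much of each look-back period falls after screening depends on the unstated minimum gap. For the 7-day plasma period it is anything from 1 day of 7 to all 7, so no fixed share is given.

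**5. Steroid rules.** Take a course of exactly 3 consecutive days.
- Synopsis: 3 ≥ 3 is true, so excluded.
- Section 4.4.2: 3 > 3 is false, so admitted.

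The disagreement can also run the other way. Two separate 2-day courses have a longest run of 2 < 3, so the synopsis admits them; their total of 4 > 3 is excluded by 4.4.2. That holds only if 4.4.2 is meant to total separate days, which it does not state.

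**The case against.** The strongest reply is that the protocol's safeguards already cover most of this, and much of that reply stands.

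- **Pregnancy.** A reader might infer that the plan breaches section 11.3 or leaves women unprotected at dose 1. It does neither. The screening test precedes the first dose, three months of prior contraception are required, and exclusion 8 also bars women planning pregnancy. This is a scheduling weakness, not a contradiction. What these safeguards do not explain is why the first dose is treated differently from the other two.
- **Eligibility.** A reader might infer that the four dosing-dated exclusions lapse after screening. They still bind, because sections 4.1 and 5.3 randomize only eligible patients. Section 6.1 speaks of a screening period, which need not be one early visit. Day 0 already has pre-dose temperature, vital signs, examination, laboratory tests and concomitant medication. Adverse events are recorded from consent (11.2, 11.4). Section 4.4.4 replaces patients withdrawn before the first dose, and section 6.6 deals with entered patients found ineligible. What remains is the absence of an explicit confirmation step and of a donation question.
- **Steroids.** A reader might infer that the five sites would apply different rules. That is unlikely: section 6.1 sends sites to 4.4.1 and 4.4.2, and the synopsis lists only main criteria, so 4.4.2 is the operative text. Nor is steroid use between screening and Day 0 left largely open. Section 4.4.3 bars high-dose use other than for relapse, inclusion 3 requires a month of neurological stability, Day 0 includes a relapse assessment, and section 7.4.4 sends a relapse coinciding with the next dose to the sponsor's medical officer.
- **Labelling.** The fever exclusion numbers the dosing day differently from Table 6-1. Section 7.3 uses the same numbering and section 7.2.5 fixes a pre-dose temperature, so this is clerical and no harm follows.

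**Conclusion.** The point holds as a modest, specific safety improvement. One dose of three, the first, has no same-day pregnancy test, and the result it relies on may be up to about 28 days old. The lower limit of about 1 to 7 days rests on an assumption about the Week -1 label. The probability of an undetected pregnancy at dose 1 cannot be derived from the protocol; given the contraception requirement it should be small.

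Two secondary points also hold. The synopsis and 4.4.2 contradict each other for a steroid course of exactly 3 consecutive days, with 4.4.2 governing in practice. Exclusions 15, 16, 17 and 22 depend on the dosing date but have no stated Day 0 confirmation, and for donation there is no Day 0 record either. Neither point implies bias between arms, a loss of patients or a threat to the analysis.

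**What to change.** 1. In Table 6-1, tick the urine pregnancy test at Day 0, before dosing, as at doses 2 and 3, using the urine already collected that day. Section 7.2.2 then needs no change because it refers to the table.
2. Add a Day 0 tick to the inclusion/exclusion row and a sentence in 6.1 saying that exclusions 15, 16, 17 and 22 are re-confirmed before the first dose from the assessments already scheduled, plus one question on donation and vaccination.
3. State one steroid rule in both the synopsis and 4.4.2, with the same course length and the same method of counting (consecutive or total days).

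Cost: wording changes in the synopsis, 4.4.2, 6.1 and Table 6-1; one dipstick per female patient, so at most 32 among the 32 planned patients, apart from replacements; and one short question to patients already in hospital. An occasional first dose will be deferred. A patient withdrawn at that stage is replaced under 4.4.4, whereas one withdrawn after dosing is not, so the check is best made before the first injection.
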